### Population

Children and young people aged 12 to 18 years inclusive will be recruited after assessment by the Bath/Bristol paediatric CFS/ME service. This is a large regional and national service that currently provides assessment and treatment for over 250 children a year. The majority of referrals are from South Gloucestershire, Bristol, Somerset and West Wiltshire. Referrals are made by paediatricians, general practitioners and, in some cases, schools. Children are given a diagnosis of CFS/ME after a thorough assessment and screening blood tests according to guidelines produced by the National Institute for Health and Care Excellence (NICE) [2]. The majority of children referred into the service have CFS/ME as other causes of fatigue are usually excluded prior to referral. Approximately 10% of children referred into the service are housebound and are assessed at home.

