### Inclusion/exclusion criteria

Children will be included if they have CFS/ME and are between 12 and 18 years old inclusive. Children will be excluded if: they are too severely affected to attend hospital appointments (defined as children and young people that do not regularly leave their house); or if they or their parents have insufficient English to either understand the patient information sheet and consent form to take part in the LP or the research interviews.

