### Interventions

•SMC: children and their families are offered a variety of treatment options that are recommended in NICE guidelines [2]. Typically this is centred around graded activity and involves a follow-up phone call at two weeks followed by family based rehabilitation consultations lasting one hour at approximately six weeks, three months, and four and a half months. The number and timing of the sessions are agreed with the child and family and varies depending on the needs and goals of the child. Children who have high levels of anxiety are offered three individual sessions of CBT every two weeks over a six week period. Other interventions such as graded exercise therapy (GET) [16] are available for children and young people if needed. The clinical team providing SMC are not informed by the research team to which trial arm a participant has been allocated.

•SMC plus the LP: in addition to the SMC detailed above, young people and their parents will be asked to read the information about the LP on the website [http://www.lightningprocess.com] or using information sheets. If the young person is well enough, they will be asked to read a book about the LP, given to them from the LP team, or listen to an audio book if preferable. Children/young people and their parents will be asked to complete an assessment form (which will take about ten minutes) where they are asked to identify their goals and describe what they learnt from reading the book. After this they will have a telephone call with a LP practitioner (usually approximately 20 minutes). This is used to check that the young person and their parents are happy about attending the course, checks the goals identified by the young person and is an opportunity for the young person and their parents to ask further questions. If the young person and their family are happy to continue, the young person will be given a date to attend a course.

•The course is three sessions on three consecutive days. Each session is three hours and forty-five minutes long. Group sessions will include three to five young people between 12 and 18 years of age who live within the region covered by the CFS/ME service. During the group, children and young people will receive a theory session and a practical session. The course is free to those participating in the trial.

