### Statistical considerations

#### Sample size

We used a definition of a clinically important difference for the SF-36 physical function subscale from three expert consensus panels for chronic diseases in adults. The panels conducted a literature search and used the Delphi technique to reach consensus on the thresholds for change over time for small, moderate and large clinically important SF-36 change scores [24]. Consensus was agreed by each panel that a small clinically important difference would be 10 as this is the equivalent to two state changes (a state change is one improvement in one item - the minimum difference between inventories). A moderate improvement was defined as 20 and a large improvement as 30.

To be able to detect a difference between the two treatment arms of 8 to 10 points on the SF-36 PCS at six months with 90% power and 1% two-sided alpha, we have calculated (using STATA) that a total of 32 to 50 participants in each arm for analysis are required. Allowing for 10 to 20% non collection of primary outcome data at six months, we aim to recruit 80 to 112 participants to the study.

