#### Data analysis

The analysis and presentation of the trial will be in accordance with CONSORT guidelines [14]. A full statistical analysis plan will be developed and agreed with the Trial Management Group and Trial Steering Committee prior to conducting any analyses.

We will use descriptive statistics to compare characteristics of invited individuals who did or did not agree to take part and eligible individuals who were randomised or not randomised. We will also examine the balance between the trial arms in participant characteristics.

The primary intention-to-treat analysis will compare the SF-36 physical function subscale at six months between groups using multivariable linear regression adjusting for baseline value of the outcome and minimisation variables, paying attention to 95% confidence intervals as well as *P*-values. Similar analyses using appropriate regression models will be conducted for secondary outcomes. Sensitivity analyses will be conducted using standard techniques to impute missing data [25], and to estimate the efficacy of the intervention among compliers.

The statistical analysis plan including subgroup analyses for the primary outcome. This will be conducted to explore differences in outcome according to age (< 14.99 versus 15.0 to 17.99), gender (male/female) and severity (no school attendance versus some school attendance) as age and gender are risk factors for CFS/ME and disease severity is a predictor of outcome. These subgroup analyses are exploratory and will be interpreted with due caution [26]. Any suggestion that the intervention effect differs according to age, gender or severity would need to be confirmed in subsequent studies. These will include interaction terms in regression models.

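### The older age subgroup stops at 17.99 although 18-year-olds are eligible, so any 18-year-old randomised has no place in the exploratory age-by-treatment analysis (minor correction)

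*Protocol article*

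**What the plan says.** Eligibility by age is stated consistently in the protocol article. The Population section says "Children and young people aged 12 to 18 years inclusive will be recruited", and the Inclusion/exclusion criteria say "Children will be included if they have CFS/ME and are between 12 and 18 years old inclusive". The Interventions section describes the courses in the same terms: "Group sessions will include three to five young people between 12 and 18 years of age". The abstract gives the same range.

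The Data analysis section then sets out three subgroup analyses of the primary outcome, by age, gender and severity. The age bands are given as "age (< 14.99 versus 15.0 to 17.99" years. On method it says "These will include interaction terms in regression models", and on status "These subgroup analyses are exploratory and will be interpreted with due caution". The bands appear nowhere else in the article.

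**The concern.** The bands for a subgroup analysis should place every eligible participant in exactly one group. These do not. With 18 included in the eligible range, a whole year of eligible age lies above the older band. A sliver just below 15.0 is also unassigned, because the younger band is written as strictly less than 14.99.

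A participant without a value on the two-level age factor cannot contribute to a model containing its interaction with treatment. Either the oldest participants, who sit at one end of the modifier under study, are left out, or someone decides at analysis where to put them. Removing that decision is the purpose of fixing the bands in advance.

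The article defers a full statistical analysis plan, but it states these cut-points itself. The issue is therefore a stated definition that conflicts with stated eligibility, and not a detail left for later. An analysis plan that copied the bands would carry the error forward.

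**Working it through.** The plan gives no count of participants per age band, so there is no figure to reproduce. The check is one of coverage, followed by a range for the number affected.

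**Inputs from the article**
- Eligible ages: 12 to 18 inclusive (Population; Inclusion/exclusion criteria).
- Younger band: age < 14.99. Older band: 15.0 ≤ age ≤ 17.99 (Data analysis).
- Recruitment: "we aim to recruit 80 to 112 participants to the study" (Sample size).

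**Assumptions**
- The share of participants aged 18 is not given, so it is shown as a range.
- Including age 18 is read as running up to the 19th birthday.

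**Step 1: coverage.** At two decimals there are 700 eligible ages, 12.00 to 18.99. Those in neither band are 14.99 (one value) and 18.00 to 18.99 (100 values), which makes 101 in all.

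**Step 2: the gap below 15.0.** Its width is 15.0 − 14.99 = 0.01 year, or 0.01 × 365.25 ≈ 3.7 days. If ages were even over seven years, the share is 0.01/7 ≈ 0.14%. That is 0.0014 × 80 ≈ 0.1 to 0.0014 × 112 ≈ 0.2 expected participants, which is effectively none.

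**Step 3: the 18-year-olds, upper end.** If ages were even from 12.0 to 18.99, the share is 1/7 ≈ 14.3%. That is 80/7 ≈ 11.4 to 112/7 = 16.0 participants.

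**Step 4: smaller shares.** The expected number is N × p. The chance of at least one is 1 − (1 − p)^N, treating participants as independent.

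| Share aged 18 (p) | Expected number, N = 80 to 112 | Chance of at least one |
|---|---|---|
| 0% | 0 | 0% |
| 1% | 0.8 to 1.1 | 55% to 68% |
| 2% | 1.6 to 2.2 | 80% to 90% |
| 5% | 4.0 to 5.6 | 98% to more than 99% |
| 10% | 8.0 to 11.2 | more than 99% |
| 14.3% | 11.4 to 16.0 | more than 99% |

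**Step 5: the alternative reading.** If the upper limit were the 18th birthday, the eligible span would be six years and only ages between 17.99 and 18.0 would be uncovered at the top. The share is 0.01/6 ≈ 0.17%, or 0.1 to 0.2 expected participants. In that case the bands are nearly complete and the eligibility wording is what needs changing.

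**Step 6: after the fix.** With bands of under 15.0 and 15.0 and over, no eligible age is unassigned under either reading.

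**The case against.** The strongest case on the other side is that little depends on this. It touches one of three subgroup analyses. The article calls them exploratory and says that any suggested difference would need confirmation in later studies. The primary comparison adjusts for the baseline value and the minimisation variables, and nothing applies these bands there. No sample size, power or main conclusion changes. All of this stands, and it is why the point is minor.

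It can also be said that the article never states that unclassified participants are dropped, and that a sensible analyst would put 18-year-olds with the older group. That is likely, but it departs from the stated upper bound, so the definition still needs correcting. Finally, the precise bound of 17.99 may show that recruitment up to the 18th birthday was intended. The explicit inclusion of age 18 in two sections speaks against this, but the article does not settle it.

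A reader might infer more than the document supports:
- **That about one participant in seven is lost.** This figure is a ceiling from an even-age assumption. Recruitment is through a paediatric service, and no age distribution is given.
- **That the intention-to-treat principle is breached.** The article attaches that term to the primary analysis only.
- **That the gap below 15.0 removes participants.** It spans about 3.7 days of age and looks like a slip of notation.
- **That age must be analysed as continuous.** Two prespecified groups contradict nothing in the article, and a continuous interaction normally assumes linearity. That choice is a trade-off and not part of this correction.

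**Conclusion.** The age bands conflict with the eligibility text. An 18-year-old can be randomised but, as written, has no value for the exploratory age-by-treatment interaction. The number affected cannot be known from the article. It is 0 to 16 participants (0% to about 14% of 80 to 112), where the upper end assumes ages spread evenly up to 18.99. Even a 1% to 2% share of 18-year-olds would make at least one such participant more likely than not.

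This rests on reading the eligible range as running to the 19th birthday. If the 18th birthday was meant, almost nobody is left out and the error lies in the eligibility wording. On either reading the sections disagree and need to be reconciled. The primary analysis is untouched, and the correction is minor.

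**What to change.** In the protocol, and in the statistical analysis plan if it repeats the bands, define the age subgroups as under 15.0 years versus 15.0 years and over. Every randomised participant then falls in exactly one group, and the gap below 15.0 closes with the same edit. If the intended upper limit was the 18th birthday, correct the age range under Population and Inclusion/exclusion criteria, and wherever else it appears, to match.

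The cost is a line or two of text, best changed before any analysis by arm. Sample size, power and the primary analysis stay as they are, and there is no downside.

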### Randomisation

The recruiting researcher will explain the rationale for the study and its design, the uncertainties about the effectiveness of either intervention, the known advantages/disadvantages of the interventions, the options available outside the RCT, and the right not to take part in the study or to withdraw at any time. Willingness to participate will be ascertained, checking that both the young person and their family understand the study. Those willing to take part in the study will be asked to consent to randomisation and sign the consent form. The recruiting researcher will then telephone the automated randomisation service operated by the Bristol Randomised Trials Collaboration for the intervention allocation, which will be conveyed to the participant. Allocation will be minimised [15] by age and gender, and retain a random component to reduce risk of prediction of allocation. If for any reason the service is unobtainable, randomisation will be completed during the next working day and the participant will be told of the results by phone or in person.

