### ‘Outcome assessment’

The following self-completed inventories will be collected at the first clinical assessment (baseline), 3, 6 and 12 months: 11 item Chalder Fatigue Scale [17]; pain visual analogue scale; physical function short form (SF-36) [18]; the Spence Children’s Anxiety Scale (SCAS) [19]; the Hospital Anxiety and Depression Scale (HADS) [20] for children aged 14 and over, and the Euroqol (EQ-5D) [21] a five-item quality of life inventory. Children and young people are asked about school attendance and home tuition in a two-item inventory. We will ask for consent to check school attendance using school records at assessment, 3, 6 and 12 months. Follow-up questionnaires will be sent in the post with a stamped addressed envelope for self completion.

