#### Primary outcome

The primary outcome will be the SF-36 physical function subscale analysed as a continuous variable collected at six months post-randomisation. The SF-36 will be scored as the sum of responses to the ten items, each of which is coded 0 for ‘Yes, limited a lot’, 5 for ‘Yes, limited a little’ and 10 for ‘No, not limited at all’. This yields a score varying from 0 (for the highest level of disability) to 100 for no disability. The SF-36 physical function subscale will be used as we are primarily interested in change in physical function. It has been used in studies of adolescent CFS/ME [22] and in CFS trials in adults [16]. We chose six months as this was the first time that all those randomised to LP and SMC will have received LP. Secondary outcome measures will be school attendance, calculated as a percentage of expected sessions, at 3, 6 and 12 months; the SF-36 (physical function) at 3 and 12 months; the Chalder Fatigue Scale score at 3, 6 and 12 months; pain visual analogue scale at 6 months and quality adjusted life years (QALYs, derived from the EQ-5D) over the 12 month follow- up period.

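### School-attendance severity, which the protocol itself calls prognostic, is neither minimised on nor in the primary model beyond what baseline SF-36 carries; pre-specifying it is a cheap gain in precision and robustness

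*Protocol article*

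**What the plan says.** All references are to the protocol article.

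- **Allocation** (Randomisation): "Allocation will be minimised [15] by age and gender", with a random component. No other factor is named.
- **Primary model** (Data analysis): six-month SF-36 physical function is compared between arms by "multivariable linear regression adjusting for baseline value of the outcome and minimisation variables". Read with the Randomisation section, the covariates are baseline SF-36 physical function, age and gender.
- **Severity** (Data analysis): one of three exploratory subgroup factors, defined as "severity (no school attendance versus some school attendance" and examined through an interaction term. The reason given for including it is that "disease severity is a predictor of outcome". Age and gender are justified only as risk factors for having the condition.
- **Collection** (Outcome assessment): the inventories are collected at the first clinical assessment and at 3, 6 and 12 months. On attendance: "Children and young people are asked about school attendance and home tuition in a two-item inventory". School records are a second source, subject to consent: "We will ask for consent to check school attendance using school records at assessment, 3, 6 and 12 months".
- **Scale of the primary outcome** (Primary outcome): "This yields a score varying from 0 (for the highest level of disability) to 100 for no disability". Its baseline value is therefore itself a measure of functional severity, and it is in the model.

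**The concern.** Apart from the baseline outcome, the one variable that the protocol describes as predicting outcome is left to chance at allocation and is absent from the primary regression. Two variables described only as risk factors for the disease are both balanced and adjusted for.

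In a trial of this size a chance difference between arms in the proportion out of school can be appreciable. Whatever that difference carries beyond baseline SF-36 passes into the treatment estimate. The protocol will examine balance between arms but ties no action to the result. If an imbalance appears, the team must either leave it or adjust after seeing the data. A covariate named in advance removes that choice and, if it is prognostic, narrows the interval.

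What is at stake is precision and protection against an unlucky allocation. Bias in the usual sense is not at stake.

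**Working it through.** **1. The plan's own sample size.** Inputs from Sample size: difference 10 or 8 points, 90% power, two-sided alpha 1%, 32 to 50 per arm analysed, 10% to 20% loss, 80 to 112 recruited. The article prints no SD, so the per-arm figure cannot be reproduced from its inputs alone.

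- Normal formula, n = 2·SD²·(2.576 + 1.282)²/d², with an assumed SD of 10: 29.8, so 30 (10 points); 46.5, so 47 (8 points).
- Two-sample t calculation, same SD: 32 and 49, close to the stated 32 and 50.
- Solving the normal formula for the SD gives 10.37 at both ends.
- Recruitment: 64/0.8 = 80; 100/0.9 = 111.1, rounded up to an even 112. This reproduces.

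Below, SD = 10 is taken as the residual SD after baseline SF-36, age and gender. This is an assumption.

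**2. Chance imbalance in severity.** The proportion p with no school attendance is not given, so 20% and 50% are assumed. Under simple 1:1 allocation the 95% limit for the difference in proportions is 1.96·√(2p(1−p)/n). The shift in the estimate is that limit times D, the assumed residual effect of severity after baseline adjustment.

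| n per arm | p | 95% limit | shift, D = 5 | shift, D = 10 |
|---|---|---|---|---|
| 32 | 20% | 19.6 pp | 0.98 | 1.96 |
| 32 | 50% | 24.5 pp | 1.23 | 2.45 |
| 50 | 20% | 15.7 pp | 0.78 | 1.57 |
| 50 | 50% | 19.6 pp | 0.98 | 1.96 |

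The range is about 0.8 to 2.5 points, against a target of 8 to 10.

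**3. Precision gained.** Let r be the partial correlation of severity with six-month SF-36 given the current covariates. The article gives no value. Adding the term multiplies the residual variance by (1 − r²) and takes the residual degrees of freedom from 2n − 5 to 2n − 6. On average, chance correlation with arm also inflates the variance by 1 + 1/(2n − 7). The net ratio of standard errors is √[(1 − r²)(1 + 1/(2n − 7))].

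| r | SE change, n = 32 / 50 | power, n = 32, 10 points | power, n = 50, 8 points |
|---|---|---|---|
| term not added | – | 90.5% | 91.2% |
| 0 | +0.9% / +0.5% | 90.5% | 91.2% |
| 0.1 | +0.4% / 0.0% | 90.8% | 91.5% |
| 0.2 | −1.2% / −1.5% | 91.8% | 92.4% |
| 0.3 | −3.8% / −4.1% | 93.3% | 93.9% |
| 0.4 | −7.6% / −7.9% | 95.2% | 95.7% |

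The power columns count the lost degree of freedom but not the average variance inflation. Putting the inflation in as well lowers each entry by about 0.2 to 0.6 points. At n = 32 the power becomes 89.9%, 91.2%, 92.8% and 94.8% for r = 0, 0.2, 0.3 and 0.4. The gains of about 1, 3 and 4 to 5 points are thus slightly favourable readings.

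Break-even is where (1 − r²)(1 + 1/(2n − 7)) = 1, that is r² = 1/(2n − 6). This gives √(1/58) = 0.13 at 32 per arm and √(1/94) = 0.10 at 50.

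**4. How steps 2 and 3 connect.** With a residual SD of 10, r = D·√(p(1−p))/10. D = 5 gives r = 0.20 (p = 20%) or 0.25 (p = 50%). D = 10 gives 0.40 or 0.50. The 2.5-point shift therefore presumes r of about 0.5, which is a strong assumption once baseline SF-36 is in the model. The two tables are two views of the same quantity and should not be added together.

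**The case against.** The strongest reply is that severity is already in the model. Baseline SF-36 physical function is a continuous measure of disability and probably the best single predictor of the six-month score. That stands, and it limits the point to what school attendance adds. A reader might infer that the plan ignores severity altogether; the Data analysis section does not support that reading.

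Second, the sentence calling severity a predictor does not say which outcome it predicts, nor that attendance predicts SF-36 given baseline SF-36. That also stands. A reader might infer that the plan is certainly giving up precision. The documents give no correlation from which to conclude this, and a small one would mean no gain.

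Third, the covariate is not free and may be incomplete. One degree of freedom is spent, the inventory is self-completed, and the records check needs consent. Attendance is asked of the participants; the article does not show that it is obtained for all of them. The fix therefore needs a rule for missing values.

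Fourth, a full analysis plan is promised and may add covariates. If it already includes severity, the point is met. But the article states the primary covariate set outright, so the choice can be commented on as it stands.

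Fifth, randomisation keeps the comparison valid, and adjusting for the baseline outcome and the minimisation factors is standard practice. Both are true, and neither bears on a suggestion about efficiency and robustness.

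**Conclusion.** The point holds as an inexpensive improvement. The protocol names school-attendance severity as prognostic, asks about it at baseline and needs it for a subgroup analysis, but neither minimises on it nor adjusts for it beyond baseline SF-36.

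The possible shift from chance imbalance, about 0.8 to 2.5 points, rests on three assumptions: 20% to 50% not attending, a residual effect of 5 to 10 points, and allocation that behaves as simple randomisation with respect to severity. The power gain rests on an assumed residual SD of 10 and an undocumented partial correlation. It is modest at 0.2 to 0.3 and absent below about 0.10 to 0.13. The downside is bounded at a 0.5% to 0.9% larger standard error.

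A reader might infer that the planned comparison is biased or that the protocol contradicts itself. Neither follows. The analysis is valid as written, and using a variable as an exploratory effect modifier does not oblige the team to use it as a covariate.

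**What to change.** Before any analysis, add baseline school-attendance severity as a pre-specified covariate in the primary SF-36 model. Use the protocol's own two levels and do not create new ones. State that a missing baseline value will be handled by a missing indicator or simple imputation, so that no child is dropped.

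Add the same term to the secondary models, except that for school attendance. By the plan's own rule that model would already adjust for baseline attendance, and a dichotomised copy would be largely redundant.

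If the team prefers the present model as primary, name the severity-adjusted model as a sensitivity analysis or give the reason for leaving it out.

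The cost is one line in the analysis plan and one degree of freedom (two with a missing indicator). No new data collection is needed.
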